### Data collection

Primary outcomes will be continuously collected every month by extracting data from the hospital information systems (HIS) and their annual reports. Secondary outcomes are collected at baseline (T_0_), 3 months after intervention (T_1_, the end of intervention), and 6 months after intervention (T_2_, follow-up). Data collection will be completed by research assistants who are not aware of this study’s design.

### Statistical methods

Statistical analysis will be performed using SPSS version 22.0 software (SPSS Inc., Chicago, IL, USA). Descriptive statistics will be reported as frequencies and percentages, if applicable. The Shapiro-Wilk test will be used in order to examine the distributions of the continuous outcomes. Quantitative variables will be presented using means and standard deviations or as the median and interquartile range. A Student’s t-test, Mann-Whitney U test, Chi-square test, or Fisher’s exact test will be adopted to compare the groups according to their normality distributions. Additionally, a repeated ANOVA will be used to explore the effectiveness of the CRSCE training program and further regression analysis will be performed, if appropriate. The statistical significance will be set at *P* < 0.05, two tailed, with a 95% confidence interval (*CI*).

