### Settings and participants

This trial will be conducted among 6 major public psychiatric hospitals in Guangdong, China. The involved psychiatric hospitals are Guangzhou Mental Health Center (GZ), Shenzhen Mental Health Center (SZ), the Third Hospital of Foshan City (FS), the Second Hospital of Huizhou (HZ), Shantou Mental Health Center (ST), and the Third Hospital of Meizhou (MZ). The number of wards (secured and non-secured) and nurses of the involved hospitals are shown in Table 1*.* This study has gained ethical approval from the IRB of GZ. Executives from the involved institutes will be informed and asked for their permission to conduct the study, with the help of the nurses. Informed consent will be obtained from all participants before they complete the surveys.

**Table 1 Tab1:** Numbers of wards and nurses of recruited hospitals (secured and non-secured)

Hospital	Non-secured ward			Secured ward		
	Number of wards	Number of beds	Number of nurses	Number of wards	Number of beds	Number of nurses
GZ	3	120	65	14	865	322
SZ	1	45	18	10	623	297
FS	1	106	29	8	816	243
HZ	1	44	20	7	906	291
ST	3	60	46	8	620	231
MZ	1	60	20	7	700	220

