### Outcomes

Primary outcomes are objective clinical indicators of the included wards, which will be extracted from the hospital information systems and their annual reports. The objective indicators include the frequency of WPV, injuries caused by WPV, and the use of coercion (physical restraint and seclusion). The objective indicators will be calculated as follows:
monthly WPV frequency = monthly numbers of WPV event / total monthly patient days × 1000 ‰;monthly frequency of injuries caused by WPV = monthly numbers of injuries caused by WPV / total monthly patient days × 1000 ‰ and;monthly frequency of physical restraint (or seclusion) = monthly numbers of patient days of physical restraint (or seclusion) / total monthly patient days × 1000 ‰.

Secondary outcomes are collected in order to evaluate the impacts on the nurses. The De-escalating Aggressive Behavior Scale (DABS), Confidence in Coping with Patient Aggression Instrument (CCPAI), Maslach Burnout Inventory-General Survey (MBI-GS), and Professional Quality of Life Scale (Pro QOL), will all be used to evaluate the capacity of DE, confidence of DE, level of job burnout, and professional quality of life, respectively. The above survey instruments will be used after obtaining licenses. The flow chart of this study is presented in Fig. 1.

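### Monthly rates per patient-day are tested as continuous values, with the test picked by Shapiro-Wilk and no stated weight, offset or ward-type term

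*Protocol article*

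**What the plan says.** Under Outcomes, the protocol article states: "Primary outcomes are objective clinical indicators of the included wards". The first is defined as "monthly WPV frequency = monthly numbers of WPV event / total monthly patient days × 1000" per mille. Injuries have the same form. Restraint and seclusion use patient-days under the measure as the numerator, so they are proportions of patient-days rather than event counts.

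Under Sample size, the planning unit is a monthly record, with 48 records from a hospital of 8 wards over 6 months. That is one record per ward per month.

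Under Statistical methods: "The Shapiro-Wilk test will be used in order to examine the distributions of the continuous outcomes". A t-test, Mann-Whitney, chi-square or Fisher test "will be adopted to compare the groups according to their normality distributions". It then adds: "a repeated ANOVA will be used to explore the effectiveness of the CRSCE training program and further regression analysis will be performed, if appropriate". No weight, offset, count model or ward-type term is named.

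Table 1 ("Numbers of wards and nurses of recruited hospitals (secured and non-secured") gives wards, beds and nurses separately for the two ward types. Neither Randomization nor Statistical methods uses that split.

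**The concern.** The article goes beyond leaving detail to an analysis plan: it names the tests and the rule for choosing among them. Three consequences follow if the tests are applied to ward-month rates.

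- **Precision.** A monthly rate from a small ward is noisier than one from a large ward. A t-test, a rank test and a repeated-measures ANOVA give both the same weight.
- **Target of estimation.** If Shapiro-Wilk rejects, the group comparison becomes a rank comparison. That gives no rate difference or ratio, although the trial is planned on a fall in a rate. The data would then decide what is estimated.
- **Ward mix.** The share of non-secured wards differs between hospitals. With six hospitals and no stated restriction on the randomization, the groups can differ in ward mix, and the named tests have no term to absorb this.

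**Working it through.** **Inputs.** Table 1 (wards and beds by hospital and type); Sample size (17.8% falling by 5.70% to 12.1%; 29 records; ICC 0.05; m = 48). Non-secured rates are not in the documents, so R, the non-secured rate divided by the secured rate, is an assumption and is varied.

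**The plan's own figure.** m = 8 wards × 6 months = 48. Design effect, reading the printed exponent as m − 1: 1 + 47 × 0.05 = 3.35. Then 3.35 × 29 = 97.15, rounded up to 98, and 98/48 = 2.04. This reproduces and confirms that a record is a ward-month. Planned relative fall: 1 − 12.1/17.8 = 0.32.

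**Spread of exposure.** The smallest average is ST non-secured, 60/3 = 20.0 beds per ward. The largest is HZ secured, 906/7 = 129.4. With Poisson counts the variance of a rate is inversely proportional to patient-days, so the variance ratio is 129.4/20.0 = 6.47.

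**Cost of equal weighting.** With a common underlying rate and Poisson counts, efficiency relative to patient-day weighting is n² / (Σb × Σ1/b), where b is beds per ward. Here n = 64, Σb = 4,965 and Σ1/b = 0.989, with every ward set to the average for its hospital and type. Result: 4,096 / (4,965 × 0.989) = 0.83, a loss of about 17%.

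**Ward mix.** Overall, 10 of 64 wards (15.6%) and 435 of 4,965 beds (8.8%) are non-secured. By hospital, non-secured wards run from 1/11 = 9.1% (SZ) to 3/11 = 27.3% (ST). Of the ten distinct three-against-three splits, the largest gap in ward share is 7/36 = 19.4% v 3/28 = 10.7%. It occurs in two splits, one of them GZ+HZ+ST v SZ+FS+MZ.

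With no training effect, the ratio of unweighted means is [(1 − s₁) + s₁R] / [(1 − s₂) + s₂R], where s₁ and s₂ are the non-secured ward shares of the two groups. The most extreme ratios over all splits, written as the lower group over the higher, are:

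| R (assumed) | equal weight per ward | weighted by beds |
|---|---|---|
| 0 | 0.90 | 0.95 |
| 0.5 | 0.95 | 0.975 |
| 2 | 0.93 | 0.96 |
| 3 | 0.87 | 0.92 |

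The planned ratio is 0.68. Bed weighting alone does not cure this. In GZ+HZ+ST v the rest, bed shares happen to balance (224/2,615 = 8.6% v 211/2,350 = 9.0%). In GZ+FS+ST v the rest they do not (286/2,587 = 11.1% v 149/2,378 = 6.3%). A ward-type adjustment is therefore needed as well.

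**False positives.** A null simulation used 1,000 runs per scenario, random allocation, Poisson counts, full beds, 30-day months, six months and no hospital effect, with 17.8 taken as a rate per 1000 patient-days (assumption). Rejection rates for the t-test (Mann-Whitney) were 5.2% (4.8%) at R = 1, 11.8% (9.2%) at R = 0.5 and 16.2% (9.8%) at R = 0.25. Monte Carlo error is about ±2 points. At an assumed 2 per 1000, the t-test gave 5.5% to 8.2%.

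**The case against.** A reader might infer that the plan ignores patient-days. It does not: "monthly numbers of WPV event / total monthly patient days" is the definition of the rate. What is unstated is any use of patient-days as weight or offset.

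Equal weighting is also inferred from the named tests. The article does not state the unit of the group comparison, and its regression clause is open. If hospital-month totals were compared, exposure would vary only 985/668 = 1.47-fold between hospitals, and most of the weighting point would go. This stands as a limit. However, the Outcomes and Sample size sections both point to wards, and the regression is conditional and unspecified.

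A reader might also infer that ward mix can pass for the planned effect. Four facts speak against that:

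- Randomization makes the imbalance chance noise rather than systematic bias.
- Ward mix hardly changes over the trial, and primary data are collected monthly, so a difference present before training would partly drop out of a baseline-to-follow-up comparison. The article does not spell that comparison out.
- The 19.4% v 10.7% split is the worst case. At R = 0.5, six of the ten splits give a difference of 2.8% or less.
- Even at R = 0 the shift is about 10% against 32%.

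The 20 and 129 beds are averages within a hospital and ward type, not sizes of known wards. Equal weighting with equal underlying rates loses precision but does not bias, and real between-ward variation would shrink the loss. Nor do the documents show that WPV counts contain many zeros: at an assumed 17.8 per 1000, a full 20-bed ward expects 20 × 30 × 0.0178 = 10.7 events a month.

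**Conclusion.** The point holds in a limited form. The stated rule lets a normality test decide whether a mean difference or a rank comparison is reported. As named, the tests use neither patient-days as weight or offset nor the ward-type split.

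Equal weighting costs about 17% of precision under Poisson counts with equal underlying rates. Ward mix could move unweighted means by up to about 10% if non-secured rates are lower. If those rates were instead three times the secured rates, the shift would be about 13%. All of these are well below the planned 32%. The simulated false-positive rates show that this noise is not reflected in the ward-month p-value, but they rest on assumed rates and no hospital effect.

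The documents do not support a claim that patient-days are ignored or that ward mix would reproduce the planned result. The point is worth correcting, and it is secondary to the fact that the named tests do not account for the six randomized hospitals.

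**What to change.** Drop the Shapiro-Wilk rule for choosing the primary test. For each hospital and period, total the events (or restraint/seclusion days) and the patient-days within ward type. Form a ward-type-adjusted hospital rate, for example by weighting the two type-specific rates with fixed patient-day shares common to all six hospitals; each hospital has at least one ward of each type. Compare three against three at hospital level on the log scale with adjustment for the baseline rate, and report rate ratios with 95% confidence intervals. A rank or permutation test should not be carried over to this level: with 20 equally likely allocations its smallest two-sided p-value is 2/20 = 0.10.

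If a count model with a log patient-day offset and a ward-type term is preferred, it must include hospital as the cluster with a small-sample correction. Without that it is not equivalent to the hospital-level comparison. Restraint and seclusion should be modelled as overdispersed proportions of patient-days.

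The cost is analysis wording. Patient-days are already needed for the rates, and ward type is already tabulated. The downside is that with six hospitals the intervals will be wider than those from ward-month tests. There are 6 − 2 = 4 residual degrees of freedom for log follow-up over baseline rates, or 3 with baseline as a covariate.

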### Sample size

Sample size estimation is based on monthly frequency of WPV. Using the study by I. et al., (2004), we set a significant change of 12.1% (decreased from 17.8% by 5.70%), alpha error of 0.05, beta error of 0.20, the estimated number (N _simple_) of monthly records is 29 per group for simple randomized control trial [47]. The intra-class correlation coefficients (ICC), explains the inflation factor of cluster randomized controlled design trial, is set as 0.05 in proposed study [48]. Based on the numbers of wards of MZ and HZ (*n* = 8), the minimum number of 6-month follow-up record (m) is 48. The sampling size of cluster randomized controlled trial (N _cluster_) is calculated as: N _cluster_ = [1 + (m^− 1^) * ICC] * N _simple_ ≈ 98. The minimum number of recruited hospitals of each group (N) is calculated as: N = N _cluster_/ m ≈ 2.04 < 3, suggesting at least 3 hospitals per group.

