### Randomization

This is a cluster randomized controlled trial. The randomization unit is every involved psychiatric hospital. Involved psychiatric hospitals will be consecutively coded from 1 to 6 by a statistician not actively engaging in this study. By using an online random number generator, hospitals will be assigned to either the intervention or control group according to a 1:1 ratio. The statistician will then inform the research coordinator of the group allocations. Afterwards, the training schedule of each hospital will be designed according to its allocation. To ensure justice, when the intervention group has completed the CRSCE-based program, and follow-up data have been collected, the control group will also receive the same CRSCE-based training.

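### Hospitals are randomised and the sample size allows for clustering, but the named analyses include no hospital-level clustering

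*Protocol article*

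**What the plan says.** In the protocol article, the Randomization section states: "The randomization unit is every involved psychiatric hospital". It adds that "hospitals will be assigned to either the intervention or control group according to a 1:1 ratio". With six hospitals this gives three per arm.

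The Sample size section counts monthly records. It introduces an ICC that "explains the inflation factor of cluster randomized controlled design trial, is set as 0.05 in proposed study", says that "the minimum number of 6-month follow-up record (m) is 48", and ends by "suggesting at least 3 hospitals per group".

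The Statistical methods section then lists Student's t, Mann-Whitney, chi-square and Fisher tests, where the last "exact test will be adopted to compare the groups according to their normality distributions". For the effect of the programme it says that "a repeated ANOVA will be used to explore the effectiveness of the CRSCE training program", with further regression left open as an option. Inference is two-sided at 5% with 95% confidence intervals. The section names no hospital effect, mixed model, cluster-robust variance or hospital-level summary, and it does not say what the unit of analysis is.

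**The concern.** The sample size accepts that records from one hospital are correlated; the stated analysis does not carry this through. Nothing in the article points to a comparison of six hospital values. The Outcomes section defines monthly indicators for the included wards and questionnaires for nurses, and the Sample size section counts monthly records.

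If the named tests are run on those units in their usual form, ordinary differences between hospitals enter the treatment contrast but not its standard error. P values are then too small and 95% intervals under-cover. This would affect the primary indicators and the nurse scales alike, in a trial whose Discussion expects the results to inform practitioners and policy makers.

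**Working it through.** **Inputs from the protocol article.** Three hospitals per arm; ICC 0.05; m = 48 records per hospital (8 wards × 6 months in the smallest hospitals); N_simple = 29 records per group; alpha 0.05 two-sided; power 80%. Wards per hospital, summed from Table 1: 17, 11, 9, 8, 11, 8 (64 in total, so 384 ward-months over 6 months).

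**The protocol's own figure.** Design effect = 1 + (48 − 1) × 0.05 = 3.35. Then 3.35 × 29 = 97.15, rounded up to 98, and 98/48 = 2.04, hence 3 hospitals per group. This reproduces.

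**Test on ward-months that ignores hospital.** True type I error = 2 × [1 − Φ(1.96/√DEFF)].

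| ICC (m = 48) | Design effect | Type I error |
|---|---|---|
| 0.001 | 1.05 | 5.5% |
| 0.01 | 1.47 | 11% |
| 0.05 (protocol) | 3.35 | 28% |
| 0.10 | 5.70 | 41% |

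At ICC 0.05 the standard error is too small by √3.35 = 1.83. A simulation (8,000 runs, 3 v 3 hospitals, normal outcome) gave 28.7% with 48 records each. With the Table 1 ward counts × 6 months it gave 33.5%, about 34%. A t-test on the six hospital means gave 5.0% and 5.2% in the same two settings.

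**Repeated ANOVA, group comparison at ward level.** Assume 8 wards per hospital, 6 months each, and all of the 0.05 ICC at hospital level.
- ICC of ward means = 0.05/(0.05 + 0.95/6) = 0.24.
- Design effect = 1 + 7 × 0.24 = 2.68.
- Type I error = 2 × [1 − Φ(1.96/√2.68)] = 23%.

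If wards also vary, with ward variance a share w of the total (assumed), the ICC of ward means is 0.05/[0.05 + w + (0.95 − w)/6].
- w = 0.1: ICC 0.171, design effect 2.20, error about 19%.
- w = 0.5: ICC 0.08, design effect 1.56, error about 12%.

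**Nurse questionnaires.** Table 1 gives 240 to 387 nurses per hospital. The article states no ICC for these scores. Under assumed values of 0.01 and 0.05, an unadjusted comparison simulated at 33% and 63% error.

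**Cost of a valid analysis.** The critical value on 4 df is 2.776. At ICC 0.05 and m = 48, the valid interval is 2.776 × 1.83/1.968 ≈ 2.6 times as wide as the unadjusted one. The standardised effect implied by N_simple = 29 is (1.960 + 0.842)/√(29/2) = 0.736 SD. The variance of the difference in hospital means is (0.05 + 0.95/48) × 2/3 = 0.0465, so the non-centrality is 0.736/√0.0465 = 3.41. Power on 4 df is about 72%, against the 80% planned.

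**The case against.** There are four fair points on the other side.

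1. Repeated ANOVA does model correlation over time within the repeated unit. A reader might infer that it treats ward-months as independent, and so apply the 28% to it. The document does not support that. The 28% belongs to an unadjusted ward-month test; the ANOVA's fault is narrower, that wards or nurses in one hospital are taken as independent.
2. The section states no unit of analysis, and a t-test on six hospital values would be valid. That the tests will be run on wards and nurses is an inference from the Outcomes and Sample size sections. It is a strong inference, because nothing points the other way. For the same reason, a reader might infer that ward rates will be compared without weights; the text says nothing on weighting, so that is no part of this point.
3. The size depends on the ICC. At 0.001 there is almost no inflation. For a group-by-time term the relevant ICC is that of change. Stable hospital differences cancel there, and the document gives no value, so the figures above cannot be carried over to that term.
4. An article condenses, and model detail may sit in an analysis plan that is not shown. This stands for detail, and it covers the vague optional regression. It does not rescue the named tests. The article commits to specific methods that in standard form contradict its own design effect, so an analysis plan would have to replace them rather than fill a gap.

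**Conclusion.** The point holds in this form: the analyses named for effectiveness include no hospital-level clustering, although hospitals are randomised and the sample size assumes an ICC of 0.05. On the protocol's own inputs, an unadjusted ward-month test has about 28% type I error (about 34% with the Table 1 ward counts). A ward-level repeated ANOVA group comparison has about 23% if all of the ICC is at hospital level, and less if wards also vary.

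These figures rest on the ICC of 0.05, on a normal outcome, and on wards being the unit analysed. At an ICC of 0.01 the unadjusted test still has about 11%. Figures for nurse scores and for group-by-time rest on ICCs that the article does not give. It would go too far to say that every named test must fail, or that error is several times 5% whatever the ICC. The section should still be corrected before analysis, because the omission reaches every primary and secondary comparison.

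**What to change.** State in the Statistical methods section that effectiveness is analysed by the unit randomised, using one of two routes. They are alternatives and will not give identical results.

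- **Hospital-level summaries.** For each hospital, compute events per patient-days, or restraint or seclusion days per patient-days, with baseline taken into account (for example as change from baseline). Compare arms by t-test on 4 df.
- **Mixed model.** Include a random hospital effect, plus ward and, for questionnaires, nurse; a baseline term or a group-by-time term; and small-sample degrees of freedom.

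Do not rely on large-sample GEE or robust standard errors with 6 clusters. Do not rely on an unrestricted permutation test either: 3 v 3 has only 20 allocations, so the smallest two-sided P is 2/20 = 0.10.

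The cost is a little more analysis work and wider intervals, about 2.6 times the unadjusted width at ICC 0.05. Power is about 72% rather than 80% for a follow-up-only comparison at the effect implied by N_simple = 29. Using baseline changes this by an amount that depends on the correlation of baseline with follow-up, which the article does not give. The protocol should state this loss of power.

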### Study quality control

All instruments used in this study have been examined for their validity and reliability. Part-time nurses are not available among the 6 involved institutes. Involved psychiatric hospitals are located in different cities of Guangdong Province, and therefore possible contamination between groups is unlikely. To improve the homogeneity of the intervention, during this study newly employed nurses of the involved institutes will be assigned to the training program and will be evaluated accordingly. Short-duration refresher courses will be monthly arranged to maintain accreditation and competency among psychiatric nurses of intervention group.

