
The outcomes of the CRSCE training program, as analyzed by this study, will present helpful and practical evidence for healthcare providers and policy makers. The primary outcome data used will be the objective indicators of WPV, extracted from hospital incident data, and this will contribute to the evaluation of the CRSCE training program. The secondary outcome will assess the influence of CRSCE training program on nurses by using questionnaires. These results will inform practitioners and policy makers as to how and to what extent CRSCE improves psychiatric nurses’ WPV coping capacities. In proposed study, we hypothesize the frequency of WPV, of injuries caused by WPV, and of coercion (physical restraint and seclusion), will be decreased because CRSCE training program would help preventing WPV in early stage. Besides, after intervention, we are expected to see the increased scores of DABS, CCPAI, and Pro QOL; and a significant decline in MBI-GS score. These might reflect CRSCE training program improves the capacity and confidence in dealing with WPV, and helps to relieve job burnout symptom.

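### A repeated ANOVA on the three-wave nurse scales would keep only nurses with all three waves; a mixed model on all available waves suits these secondary outcomes better

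*Protocol article*

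**What the plan says.** All references are to the protocol article.

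- **Waves.** Data collection: "Secondary outcomes are collected at baseline" (T0), again at the end of the three-month intervention (T1), and six months after it (T2). Outcomes lists four scales: DABS, CCPAI, MBI-GS and Pro QOL. The Discussion confirms their role: "The secondary outcome will assess the influence of CRSCE training program on nurses by using questionnaires".
- **Method.** Statistical methods: "Statistical analysis will be performed using SPSS version 22.0 software". On the effect of the programme it says "a repeated ANOVA will be used to explore the effectiveness of the CRSCE training program and further regression analysis will be performed, if appropriate". It also says "A Student’s t-test, Mann-Whitney U test, Chi-square test, or Fisher’s exact test will be adopted to compare the groups", without naming an outcome, a wave or a set of nurses.
- **Later entrants.** Study quality control: "newly employed nurses of the involved institutes will be assigned to the training program and will be evaluated accordingly".
- **Training load.** Table 2 totals 36 h for routine training and 140 h for routine plus CRSCE training. Study quality control adds monthly refresher courses in the intervention group.

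The article gives no figure for nurse turnover or non-response.

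**The concern.** Classical repeated-measures ANOVA takes one row per subject and needs a value in every column. A nurse who leaves, is on leave or does not answer at T1 or T2 is removed altogether, including the scores that she did give. The comparison then describes nurses who were present and responsive at three points over about nine months (3 months of training plus 6 of follow-up).

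Two features of this trial make that more than a loss of precision.

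- **Loss may depend on the outcome.** The Background links exposure to violence with sick leave, doubts about being suited to the job, burnout and poorer professional quality of life. The last two are measured as outcomes here, and both are plausible reasons to leave or not to respond.
- **Loss may differ by arm.** The intervention asks far more of nurses' time. If that changes who stays or answers, the completers in the two arms are no longer comparable, even though the hospitals were randomised.

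**Working it through.** The plan states no figure on this point that could be reproduced. Its sample-size section counts monthly violence records, not nurses. The check is therefore one of logic, plus an illustration under stated assumptions.

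**1. Number of nurses (Table 1, non-secured + secured)**

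- GZ 65 + 322 = 387; SZ 18 + 297 = 315; FS 29 + 243 = 272
- HZ 20 + 291 = 311; ST 46 + 231 = 277; MZ 20 + 220 = 240
- Total: 387 + 315 + 272 + 311 + 277 + 240 = 1,802

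This is the staff count. Using it assumes that all of them take part and answer at T0.

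**2. Does the method need all three waves?** Yes, in its classical form. As a check, a standard repeated-measures ANOVA routine (not SPSS) was given 20 simulated subjects, three without T0 and three without T2. It refused the data as unbalanced. SPSS's repeated-measures procedure instead deletes such subjects listwise.

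**3. How many would be dropped?** Let p be the share missing at each of T1 and T2 (assumed). If the same nurses miss both waves, as when a nurse leaves before T1, the share dropped is p. If the two waves are missed independently, it is 1 − (1 − p)².

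| p (assumed) | Same nurses miss both | Independent |
|---|---|---|
| 5% | 5%, about 90 | 1 − 0.95² = 9.8%, about 176 |
| 10% | 10%, about 180 | 1 − 0.90² = 19%, about 342 |
| 15% | 15%, about 270 | 1 − 0.85² = 27.8%, about 500 |

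The range is therefore about 5% to 28% of 1,802.

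**4. What bias could follow?** Take all nurses in post at T0 as the target. Suppose that dropped nurses differ from completers by d SD, equally in both arms, and that the arms lose shares a_I and a_C. The completer mean is off by a × d within each arm, so the between-arm difference is off by (a_I − a_C) × d. Both d and the losses below are assumed.

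| Loss, one arm v the other | d = 0.3 | d = 0.5 |
|---|---|---|
| 5% v 5% | 0 | 0 |
| 10% v 5% | 0.015 SD | 0.025 SD |
| 20% v 10% | 0.03 SD | 0.05 SD |
| 20% v 5% | 0.045 SD | 0.075 SD |

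Equal loss gives zero only because d is taken as equal in the two arms.

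**5. Training load.** 140 − 36 = 104 h, which matches the 104 hours stated under Interventions. This makes differential loss plausible but does not show it.

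**The case against.** **The target and the complete-case rule are inferred.** Statistical methods does not tie the ANOVA to the questionnaires, and the monthly rates are repeated measures too. This stands as a limit. The three-wave scales are still the natural target, and no other method is linked to effectiveness. The regression is conditional and unspecified.

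**Missing-data rules belong in an analysis plan that is not shown.** This is fair as far as it goes: the absence of a rule for leavers is no finding. The point here is narrower. The article does name a method, and that method handles incomplete waves worse than an equally available alternative.

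**Stronger readings are tempting but not supported.**

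- A reader might infer that the exclusion of new hires is itself the harm. It is not. They join after allocation, so the main comparison is better made among nurses in post at T0. The sentence on evaluating them may also mean a competency check or a personal baseline at hire; it does not say that they enter the T0 to T2 analysis.
- A reader might infer that t-tests at each wave would include new hires, so that two analyses would cover different people. No wave, outcome or population is named for those tests.
- A reader might infer that new hires in control hospitals would receive CRSCE during the trial. Interventions gives controls routine training only, and Randomization gives them CRSCE only once follow-up data have been collected. What remains is loose wording.

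**The loss figures do not measure harm.** Correct. They are assumed, losses overlap for leavers, and the illustrative bias is small.

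**Conclusion.** The concern holds for the secondary outcomes. If the repeated ANOVA is applied to the four scales in its classical form, nurses without all three waves are lost, and the result describes those who stayed and answered. Under assumed missingness of 5% to 15% per follow-up wave, that is about 5% to 28% of 1,802 nurses. The low end applies if the same nurses miss both waves, the high end if misses are independent.

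The direction and size of any bias cannot be found from the document. It is near zero if loss is equal by arm and leavers differ alike in both arms. In the scenarios tried it reaches at most 0.075 SD, at 20% against 5% loss. A reader should not take from this that the trial is shown to be biased, or that its primary outcomes are affected: those are monthly rates from hospital records. The change is worth making because it is cheap and replaces a stated method with a better one.

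**What to change.** For DABS, CCPAI, MBI-GS and Pro QOL, replace the repeated ANOVA with a linear mixed model that uses all available waves among nurses in post at T0.

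- **Outcome and baseline.** Either treat T0, T1 and T2 all as responses, or model T1 and T2 with T0 as a covariate. Do not do both, since T0 would then be response and covariate at once.
- **Terms.** Arm, wave and arm × wave as fixed effects; nurse and hospital as random effects.
- **Few clusters.** Use a small-sample degrees-of-freedom correction. With six hospitals in two arms, a between-hospital comparison has about 6 − 2 = 4 degrees of freedom.
- **Missing data.** The model is valid under missing at random. It does not cure loss that depends on unobserved scores, so add a sensitivity analysis for outcome-dependent loss, such as shifted imputed values, and report loss by arm and wave.
- **Later hires.** Report nurses hired after T0 only in a sensitivity analysis.
- **Wording.** Reconcile the reference to the training programme for new hires in Study quality control with Interventions and Randomization, so that it is clear which programme is meant in each arm.

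The cost is somewhat more analysis work and an explicit reliance on missing at random. No new data are needed.
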